## Abstract

**Background:**

Chronic low back pain is a common chronic condition whose treatment success can be improved by active involvement of patients. Patient involvement can be fostered by web-based applications combining health information with decision support or behaviour change support. These so-called Interactive Health Communication Applications (IHCAs) can reach great numbers of patients at low financial cost and provide information and support at the time, place and learning speed patients prefer. However, high attrition often seems to decrease the effects of web-based interventions. Tailoring content and tone of IHCAs to the individual patient ´s needs might improve usage and therefore effectiveness. This study aims to evaluate a tailored IHCA for people with chronic low back pain combining health information with decision support and behaviour change support.

**Methods/Design:**

The tailored IHCA will be tested regarding effectiveness and usage against a standard website with identical content in a single-blinded randomized trial with a parallel design. The IHCA contains information on chronic low back pain and its treatment options including health behaviour change recommendations. In the intervention group the content is delivered in dialogue form, tailored to relevant patient characteristics (health literacy, coping style). In the control group there is no tailoring, a standard web-page is used for presenting the content. Participants are unaware of group assignment. Eligibility criteria are age ≥ 18 years , self- reported chronic low back pain, and Internet access. To detect the expected small effect (Cohen’s d = 0.2), the sample aims to include 414 patients, with assessments at baseline, directly after the first on-page visit, and at 3-month follow-up using online self-report questionnaires. It is expected that the tailored IHCA has larger effects on knowledge and patient empowerment (primary outcomes) compared to a standard website. Secondary outcomes are website usage, preparation for decision making, and decisional conflict.

**Discussion:**

IHCAs can be a suitable way to promote knowledge about chronic low back pain and self-management competencies. Results of the study can increase the knowledge on how to develop IHCAs which are more useful and effective for people suffering from chronic low back pain.

**Trial registration:**

International Clinical Trials Registry DRKS00003322

## Background

Chronic low back pain (CLBP) is a very prevalent and disabling public health problem with a significant burden on individuals, and negative social and economic effects [1]. The prevalence of CLBP is rising, the percentage of people living with CLBP more than doubled between 1992 and 2006 [2], estimates suggest that up to 12% of people experience CLBP [3] in the past 12 months. CLBP is one of the most common causes for disability [4] and results in high total expenses for the health care system [5].

Active patient involvement is a key component of effective treatments of CLBP and is equally demanded by patients, practitioners, scientists and politicians. There is a general call for more involvement in the making of medical decisions in recent clinical practice guidelines as well as for active involvement in the management of CLBP, due to important trade-offs between potential benefits, harms, costs and burdens of alternative therapies [6]. Two main aspects of patient involvement are self-management and involvement in medical decisions. Patients have to make decision regarding life style changes, medications, and use of different health services or medical interventions. Both for the involvement in medical decisions and for self-management patients need to be informed about their disease, its course, and the treatment options at hand, including their advantages and disadvantages. Providing disease-specific information to patients with CLBP e.g. can lead to better adherence to different kinds of self-management strategies [7,8]. However, due to limited resources in health care, large numbers of patients still do not have access to feasible information on CLBP.

Because of emerging Internet penetration, the ehealth tools are one current option to spread health information to a great quantity of patients with low financial burden, taking into account individual preferences with regard to time, place and previous levels of knowledge. Small but consistent effects on clinical outcomes [7-9] could be shown in trials of soundly developed online health interventions even in older populations who are expected to use the web less often [10]. Similar effects of ehealth interventions can also be shown for patients with CLBP [9-12]. There is a broad range of interactive technologies which can be used to deliver health information. Murray et al. [11] found that “Interactive Health Communication Applications” (IHCAs), a format that combines health information with at least one other type of support, e.g., social support, decision support, or behaviour change support, can have positive effects on knowledge, social support, clinical, and behavioural outcomes.

However, high attrition rates impair the effectiveness of those online applications [12,13], and often health intervention websites are not often used more than once [14,15]. Since at the same time the impact of ehealth tools increases with usage rates [15,16], the intended outcome can be influence positively if users work longer and more intensely with the information provided [17,18] and use the website more often [19,20]. A preference-sensitive provision of information as well as an interactive presentation can lead to greater individualization and personalization which has been found to increase the usage and effectiveness of web-based health information tools [21,22]. The so-called concept of individual tailoring includes these strategies [23].

### Aims of the trial

The study evaluates an IHCA with information on chronic low back pain (CLBP), pain management education and decision support in a dialogue-based, tailored format against a standard website showing identical information without dialogue or tailoring. The primary hypothesis is that the dialogue-based, tailored format has larger effects on CLBP knowledge and patient empowerment than the standard website. Exploratory research questions are if usage is higher for the dialogue-based, tailored format and whether users feel better prepared for the consultation and, when facing a health decision, experience less decisional conflict after using the dialogue-based, tailored site rather than the standard website.

## Methods/Design

### Study design

In line with a comparable study [13] of our research group, a single-blinded two-armed randomised controlled trial (RCT) with a parallel design was chosen. Outcome measurements are planned before starting to use of the IHCA, after using the system and at three month follow-up. Knowledge about CLBP (primary outcome), decisional conflict, and preparation for decision making (secondary outcomes) are assessed immediately after using the system. Patient empowerment (secondary outcome) is assessed three months after the first visit (see Figure 1).

**Figure 1 F1:**
[figure not shown]
Study procedures.

### Treatment allocation

Participants are informed within the informed consent that a random assignment to one of two website styles (dialogue-based, tailored vs standard) but with the same content will be made. The two web pages are not marked, consequently participants have no indications whether being in the control or intervention group. A specific software is used for randomisation.

### Recruitment

Health care for chronically ill people in Germany is divided into different sections, predominantly in in-patient rehabilitation centres and clinics for acute care, and out-patient primary care and specialist practices (orthopaedics, pain management). Health insurances mainly finance acute care in inpatient settings, primary care practices, and in specialist practices, whereas pension funds usually pay for treatment in rehabilitation clinics. As the inclusion of patients from all sectors was a primary study goal, patients were recruited over the whole spectrum of health care in Germany: via health insurance companies, pension funds, primary care and specialist practices, hospitals and rehabilitation centres, and self-help groups. Public dissemination strategies of the study included media such as newspapers, magazines, patient websites, and flyers. Further information on the study and the intervention can be found on the study website http://www.entscheidungshilfe.info.

### Study population

Eligibility criteria are age ≥ 18 years, access to the Internet, and self-reported CLBP (pain in the lower back almost every day for more than 12 weeks [19].

### Description of the intervention and control condition

The tailored IHCA as well as the standard website show essential information on CLBP (physiology of pain, acute vs. chronic pain, chronification, epidemiology, psychological aspects, coping and pain management) and related psychological problems (depression, anxiety), diagnostic procedures, and treatment options (pharmacological and non-pharmacological, see the list of the "IHCA's chapters and sections"). The website was designed similar in both conditions with regard to colours, typing, figures and pictures. All participants receives a password when signing in to the website via e-mail which can be used to log into the system as often as necessary.

### IHCA`s chapters & sections

•Introduction: What is this website?

• Where does the information on this site come from?

•CLBP Basics

• Physiological basics: back, spine, and intervertebral discs

• What exactly is pain?

• What is the difference between acute and chronic pain?

• Why does the pain stay when the physical injury heals?

• How many people live with CLBP?

• Managing CLBP in everyday life

•How is CLBP diagnosed?

• How much diagnostics makes sense and at which point?

• Diagnostic options

•How is CLBP treated?

• How much treatment makes sense and at which point?

• What is the natural, untreated course of CLBP?

• Are there accompanying conditions or sequelae of CLBP?

• Treatment options

•How do I recognize good treatment?

•Summary

•Additional information and literature

• Associations and self-help

• Web sites

• Journals

• Books

•Glossary

•Legal notice

•References

#### Intervention condition

The format of the website in the intervention condition tries to imitate a real conversation (dialogue-based) with a health professional, tailoring the content and tone of the dialogue to relevant patient characteristics. tunnelled design where the user proceeds through the content with a predetermined chronology was implemented in the intervention condition because such a design found to increase website use and knowledge gained from a website [20]. However, a tunnelled website might also evoke resistance [21], which is why we decided to give the user some degree of freedom over the chronology through the dialogue. Each information block ends with questions where the user can choose one of at least three reply options and receives a tailored answer. These tailored answers reflect the option the user has chosen using an empathic and appreciative intonation and build a personalized bridge to the next information block.

The concepts of coping style according to the avoidance-endurance model (AEM) [22] and health literacy (CLBP knowledge and preferred detailedness of information) were used for tailoring the provided information to individual preferences of the users. The individual coping style was assessed by using a questionnaire which is presented before starting the dialogue. There are four AEM subtypes: the “depressed endurer” (high endurance coping (EC) and high depressiveness (D)), the “happy endurer” (high EC and low D), the “depressed avoider” (low EC and high D), and the “adaptive coper” (low EC and low D; for examples see Table 1). During the virtual conversation, the content, the intonation and messages are tailored to the coping style of the individual user. This approach was inspired by Motivational Interviewing [23], a counseling technique used especially to address ambivalence about health behavior change.

**Table 1 T1:** Tailoring to coping style

**Coping type**	**Adaptive coper**	**Happy endurer**	**Depressed endurer**	**Depressed avoider**
Description of coping style	You go about your pain in a matter-of-fact manner. You know that, on one hand, there is no serious disease behind it but that, on the other hand, they can signal you physical strain. You are good at making short breaks at the right time in order to keep up your daily routine – maybe temporarily a little slower than usual.	You tend to keep going in your daily routine even if pain is strong. This is, on one side, a personal strength. But at the same time you run the risk of actually straining your muscles, ligaments, joints and intervertebral discs.	You are a multitasker. Saying “No” to someone or not getting things done is hard on you. In order to meet requirements and get things done you push yourself to your limits and beyond. Often you don´t listen to your body before it is overstrained.	You are unsettled by your pain. You are worried that there might be a serious disease behind it, and / or you avoid activities that might increase the pain.
Take home message	Keep on like that! Make exercise part of your routine if you haven´t done it yet. Choose something fun and back-friendly. If you strengthen your muscles and stick to your relaxing breaks the pain should vanish soon.	Even if it´s hard: Try to pay more attention to your pain and get breaks early enough. Keep working, do things that are pleasant and fun, and keep moving – but remember to pause when you might need it!	Reconsider what you are asking from yourself: Do you really have to demand so much? Maybe there are times when it is possible to leave something undone, do it o.k. instead of perfect, or ask for assistance. These things are closely related to your pain.	Pain is unpleasant but not dangerous. Don´t let it suffocate you. Expand your limits step by step, and make pleasant activities a part of your everyday life.

The items that assess CLBP knowledge are presented during the dialogue: In the beginning of the respective section (e.g. physiological basics), the user is questioned about his level of knowledge on this subject. Depending on the response, the subsequent section is accordingly amended. Figure 2 shows an exemplary dialogue window.

**Figure 2 F2:**
[figure not shown]
Dialogue window.

#### Control condition

For the control condition (using a standard website), no tailoring occurs for the provided information and the content is not offered using a predetermined chronology with a dialogue format and no guidance for the users throughout the content occurs. Using a classical webpage design, on each page a site map shows each content section which the user can chose by clicking on it to be forwarded to the selected content (see Figure 3).

**Figure 3 F3:**
[figure not shown]
Control window.

### Potential risk for participants

Contraindications or side effects of IHCAs are not known.

### Intervention development and trial design

The intervention was developed in consideration of user-specific needs, the provided information is evidence-based. At the end of the development, a peer-review process was used to evaluate the system. First, a needs assessment was carried out to get insight into relevant topics for patients with CLBP. For this purpose, initially semi-structured interviews with five physicians (all specialized in orthopaedics) and nine patients with CLBP were conducted. Subsequently, we developed a questionnaire for potential users based on the results of the qualitative interviews, which should then be filled in by a new and larger patient sample (N = 117) with CLBP. The process and the results of needs assessment will be published in more detail elsewhere.

Primary sources for evidence-based information were treatment guidelines [19,24,25] and Cochrane Reviews [26-31]. In the course of developing the webpage, the selected health information was reviewed using an iterative process and interdisciplinary advisory group. After completion of the IHCA, four patients with CLBP and eight practitioners (5 orthopaedists, 1 neurologist, 1 medical journalist, and 1 psychologist) audited the system. Taking into account this feedback, the system was finalized and last modifications took place. The complete development process will be published in more detail elsewhere.

### Outcome assessment

CLBP knowledge (assessed after the first visit) and patient empowerment (assessed at three month follow-up) serve as primary outcomes. The level of knowledge about CLBP is tested with 29 statements about CLBP. The questions were developed in order to map the content covered in the sections of the IHCA. The questions can be answered with true / false / I don´t know. The Health Education Impact Questionnaire (HeiQ) [32,33] is used to assess patient empowerment. The HeiQ includes 42 items and 8 dimensions: Positive and Active Engagement in Life, Health Directed Behavior, Skill and Technique Acquisition, Constructive Attitudes and Approaches, Self-Monitoring and Insight, Health Service Navigation, Social Integration and Support, and Emotional Wellbeing. Schuler and colleagues [34] did the translation of the questionnaire into German and analysed the psychometric properties (Raykov’s Composite Reliability Coefficient, factorial and concurrent validity). The eight scales could be replicated, the questionnaire was found to be a reliable and valid measure. The dimension Social Integration and Support were removed since no effects of the IHCA were expected on these two dimensions and to keep the burden for the users at a minimum.

The shared decision-making concepts “decisional conflict” and “preparation for decision making” are used as secondary outcomes. Decisional conflict a state of uncertainty especially about medical decisions and is determined with the Decisional Conflict Scale (DCS) by O´Connor [35], a self-report instrument which measures personal verbalizations of uncertainty in choosing options. The questionnaire also measures factors contributing to uncertainty such as feeling uninformed, unclear about personal values and unsupported in decision making. It also assess the outcome of effective decision making with regard feeling the choice is informed, values-based, likely to be implemented and expressing satisfaction with the choice. The reliability of the measure is seen to be good with a Cronbach´s α between 0.78 and 0.92 [35], acceptable discriminant validity could be found. The Preparation for Decision Making Scale (PDMS) [36] is used for evaluating decision making processes relating to preparation for decision making. This 11 item scale assesses a patient´s view of how helpful a decision support intervention was in preparing for the next consultation with the practitioner and for making a treatment decision together with the practitioner. Reliability is very good ranging from α = .92 to α = .94. Both questionnaires are presented only to users who at the beginning of the survey stated that they probably will be making a treatment decision concerning their CLBP. In order to avoid missing data, all questionnaires include validation checks that alert participants when their answers are implausible or items are skipped.

### Statistical analyses

To empirically test the hypotheses, t-tests for independent samples will be calculated. We do not expect confounding factors due to randomizing the participants to the control and intervention condition and the most likely resulting structural equality of these two groups. In case baseline disparities should be detected, they will be taken account of as confounding variables in an analysis of covariance (ANCOVA). By using an intention-to-treat approach in which participants were analyzed in their original randomized groups regardless of the frequency or duration of website use we will include all randomized participants in the analyses in order to avoid biases such as non-random attrition of participants. Additionally we will perform a sensitivity analysis following the per-protocol approach. This will be done by including only participants that have completed all the measurements. A α level of ≤ 0.05 will utilized as the cutoff for statistical significance. With regard to the exploratory research questions, we expect only small sample sizes, hence only a small fraction of the participants will be confronted with the situation of having to make a treatment decision in the course their CLBP. Therefore, only these participants can be asked to fill in the DCS and PDMS. In order to be able to appraise the exactitude of testing, 95% confidence intervals will be defined for all parameters.

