### Power calculation

On the basis of the Cochrane review by Murray et al. [37] we expect a small effect on the primary outcomes (Cohen’s d = 0.2). To detect a small effect with an α of 0.05 a power of 0.80 (one-tailed t-test), a sample size of N = 310 (155 per group) is required. Expecting a dropout 20% between registration and follow-up (3 months), we aim at including a sample of N = 414 at baseline.

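### Two outcomes are called primary, but there is one 0.05 cutoff, no success rule and no single empowerment test, so the stated 5% error and 80% power do not hold together for the primary hypothesis

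*Protocol article*

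**What the plan says.** All references are to the protocol article.

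- **Primary hypothesis (Aims of the trial).** The tailored format is expected to have "larger effects on CLBP knowledge and patient empowerment than the standard website".
- **Status of the outcomes.** The Abstract, Outcome assessment and Discussion list knowledge and empowerment as the primary outcomes. Study design labels knowledge primary and empowerment secondary.
- **Tests (Statistical analyses).** "To empirically test the hypotheses, t-tests for independent samples will be calculated". The cutoff is given once: "A α level of ≤ 0.05 will utilized as the cutoff for statistical significance". There is no alpha split, test order or rule on whether one or both outcomes must be significant.
- **Empowerment measure (Outcome assessment).** "The HeiQ includes 42 items and 8 dimensions". No total score or lead scale is named. One dimension, Social Integration and Support, is then named as dropped, but the stated reason is that dimensions "were removed since no effects of the IHCA were expected on these two dimensions". Seven or six scales therefore remain.
- **Sample size (Power calculation).** One calculation covers the primary outcomes: Cohen's d of 0.2, one-tailed t-test, alpha 0.05, power 0.80, from which "a sample size of N = 310 (155 per group) is required".

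**The concern.** A single 0.05 cutoff controls the error of one test. With two primary outcomes, what the trial delivers depends on a decision rule that the article does not give.

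- If either outcome is enough, the error for the primary claim exceeds 5%.
- If both are needed, the error is controlled, but the power to support the hypothesis is lower than the power of a single test.

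The sample size rests on one test at 0.05 with 80% power, so it describes neither situation.

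The HeiQ makes this worse. With six or seven candidate scales and no test named, the empowerment result could be chosen after the data are seen, or several scales could each be reported as primary. The conflict over whether empowerment is primary at all leaves the same room for a later choice.

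**Working it through.** **Inputs from the article.** Alpha 0.05; independent-samples t-tests, one-tailed in the power calculation; d = 0.2; 155 per group stated; two primary outcomes in most sections, one in Study design; seven or six retained HeiQ scales.

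**Assumption.** The article gives no correlations between outcomes. The range 0 to 0.7 is used.

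**1. The plan's own sample size.** n per group = 2 × (1.645 + 0.842)² / 0.2² = 2 × 6.18 / 0.04 ≈ 309, or 310 with the exact t-test. So 310 is the number per group (620 in total), not the total. At 155 per group, power for one outcome is about 54% one-sided. This is a separate error in the Power calculation section. It matters here because it must not be counted as a multiplicity effect.

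**2. Two primary tests, either suffices.** For independent tests the familywise error is 1 − 0.95² = 9.75%. For correlated normal test statistics:

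| Correlation | One-sided | Two-sided |
|---|---|---|
| 0 | 9.8% | 9.8% |
| 0.3 | 9.3% | 9.5% |
| 0.5 | 8.8% | 9.1% |

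**3. Each retained HeiQ scale tested as primary, any one suffices.** The independence values are 1 − 0.95⁷ = 30.2% (knowledge plus six scales) and 1 − 0.95⁸ = 33.7% (knowledge plus seven). With correlation:

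- *All tests equally correlated, one-sided.* Seven tests: 24.5%, 20.3% and 15.9% at r = 0.3, 0.5 and 0.7. Eight tests: 26.7%, 21.9% and 16.8%.
- *Knowledge only weakly correlated (0 to 0.2) with scales that correlate among themselves at 0.3, 0.5 or 0.7; one- and two-sided, 1,000,000 draws.* Six scales: about 25-28%, 22-25% and 18-21%. Seven scales: about 27-31%, 24-27% and 19-22%.

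Across both patterns, the range for correlations of 0.3 to 0.7 is about 16% to 31%.

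**4. Both outcomes required, one test each.** The error is at most 5%, because the claim is false as soon as one outcome has no effect, and that outcome's test rejects at most 5% of the time. Joint power, if d = 0.2 holds for both outcomes (one-sided):

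| Per group | Each outcome | Joint, r = 0 | Joint, r = 0.5 | Joint, r = 0.7 |
|---|---|---|---|---|
| 310 | 80% | 0.80² = 64% | 69% | 71% |
| 155 | 54% | 0.545² = 30% | 38% | 42% |

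The 310 row isolates the effect of requiring both. The 155 row also contains the sample-size error from step 1.

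**5. Holm on two primaries.** The smaller p-value is tested at 0.05 / 2 = 0.025. At one-sided 0.025 and 155 per group, power per outcome is about 42%, against 54% at 0.05. The number per group for 80% power at that step is about 393, against 310.

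**The case against.** **The hypothesis joins the outcomes with 'and'.** If that means both must be significant, there is no inflation across the two. This stands: the error figures in steps 2 and 3 depend on an either-suffices rule that the article does not state. It does not rescue the plan, because joint power is then below 0.80.

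**Study design calls empowerment secondary.** If that section governs, one primary test at 5% remains and the multiplicity problem disappears. The Abstract, Aims, Outcome assessment and Discussion all say otherwise, but the conflict has to be settled first.

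**Stronger readings.** A reader might infer that the false-positive rate simply is 34%. The article does not support that. It does not say that each scale gets its own primary test, it leaves open whether seven or six remain, and scales from one questionnaire are likely to be positively correlated. A reader might also infer that the HeiQ has no single score. The article shows only that none is specified. Finally, a joint power of 30% should not be blamed on multiplicity. It uses 155 per group, where one outcome alone already misses 80%, and it assumes independence. In addition, knowledge is measured after the first visit, before follow-up dropout, so up to 207 per group (414 / 2) could contribute to that test.

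**Alpha sharing and scoring may sit in a document not shown.** That is fair as far as it goes, and a single cutoff does not rule out a later familywise procedure. But this article does fix the alpha, the tests and a sample size derived from one test at that alpha. The conflicting status of empowerment and the mismatch in the removed dimensions are contradictions in the text, not omissions.

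**Conclusion.** The point holds in conditional form. As written, the plan has no route that gives both 5% error and 80% power for a primary hypothesis about two outcomes.

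- **Either of two tests suffices:** error about 9-10%, for correlations of 0 to 0.5.
- **Each retained HeiQ scale tested as primary, any one suffices:** about 16-31% for assumed correlations of 0.3 to 0.7. The 34% figure is the ceiling, for eight independent tests. Separate testing is a possibility that the text leaves open, not something it states.
- **Both required, one test each:** error at most 5%, but joint power 64-71% for correlations of 0 to 0.7, even at 310 per group.
- **Empowerment secondary:** one primary test at 5%, and no multiplicity problem.

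Which case applies cannot be read from the article. That should be settled before outcome data are seen by group.

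**What to change.** 1. Reconcile Study design with the Abstract, Aims, Outcome assessment and Discussion on whether empowerment is primary or secondary.
2. Correct the sentence on removed HeiQ dimensions so that the number matches the names, and list the retained scales.
3. If both outcomes stay primary, name one pre-specified empowerment test and report individual scales as secondary. The mean of the standardised retained scales is one option. The article reports psychometric support for the separate scales, not for such a composite, so the choice needs a short justification.
4. State the success rule: either Holm across the two primaries, or both significant at 0.05.
5. Restate the power under that rule, together with the correction of the per-group sample size.

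**Cost.** The text changes are small, but the power cost is not negligible. With Holm, the first step at 0.025 lowers power per outcome for d = 0.2 at 155 per group from about 54% to 42% one-sided, and 80% power at that step needs about 393 per group rather than 310. Requiring both outcomes avoids the stricter alpha but accepts the lower joint power shown above. Under either rule, single HeiQ scales can no longer be claimed as primary results.
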